### Enrollment, Supportive PDH Intervention, and Follow-Up

The 6800 community-residing elderly adults will be screened and enrolled by the investigators according to the inclusion and exclusion criteria. To ensure the balance and representativeness of sample sources, we intend to adopt a multi-stage sampling method. At the first stage, four cites will be randomly selected in Liaoning province by randomized sortition. At the second stage, one district and one township will be randomly selected from each selected city. At the third stage, one urban community and one village community will be randomly selected from each selected district/township. At the fourth stage, elderly residents will be selected from each selected urban community and village community with a convenient sampling method.The 60 community-residing elderly adults with LLD and their principle caregivers will be allocated to trial and control groups. In addition, we will ensure that there are no statistical differences between the two groups in term of the degree of depression, drug treatment programs, knowledge of mental health, geographic distribution, and other aspects before carrying out the interventions. The trial group of 30 elderly patients and their principle caregivers will receive the same content and frequency of individualized and group intervention for 6 months. By contrast, the 30 elderly patients in the control group and their principle caregivers will receive TAR, which are suitable for all MDD patients as routine. During this period, except for any additional treatment for comorbid physical diseases or short-lasting benzodiazepines for severe insomnia, other antipsychotic medications, systematic psychotherapy, and long-lasting benzodiazepines will not be allowed. The detailed content, forms, and methods of the supportive PDH intervention are listed in **Table 2**.

**Table 2 T2:** Content, form and method of supportive PDH interventions.

	Supportive PDH interventions
Content	P: Supportive psychosocial intervention Supportive therapy, including the application of listening, sympathy, comfort, and guidance, constructive and instructional language, asking patients to actively communicate with themselves and intervention team members. Cognitive behavioral therapy, including the correction of abnormal cognition and behavior, and guiding patients to correctly face major stressful events in life or attitudes and treatment skills in the event of recurrence. Social skills training, including self-care skills training, interpersonal skills training (e.g., positive communication with family members, and active participation in related group activities). Mindfulness therapy, including breathing, mindfulness, and walking. Interest cultivation, including encouraging patients in the trial group to participate in outdoor sports therapy and entertainment therapy (e.g., painting, carpentry, clay, knitting, chess, card games, etc.), and cultivating personal interests. Group nostalgia therapy, including guiding patients to recall old classic songs, movies, important events, happy childhood events, and achievements made in life or at work. D: Supportive drug treatment Patients will be guided to use drugs strictly in accordance with a safe and standardized system. Principle caregivers will be normatively urged to provide supervision to improve the medication compliance of the patients. H: Supportive health education Mental health education, including symptoms, early signs of recurrence and preventive measures of LLD. Drug treatment health education, including knowledge about drugs (e.g., antidepressants), the importance of maintaining and taking medicine on time, the significance of pharmacotherapy for preventing recurrence and deterioration, and self-management skills for drug therapy. Lifestyle health education, including establishing a reasonable and balanced diet, good sleep hygiene, quitting smoking, limiting alcohol, and adhering to a moderate exercise regime.
Form	P: Supportive psychosocial intervention Rely on the platform of CHS to carry out group psychological intervention for patients. Rely on the family, and have intervention team members work with the principle caregivers to provide psychological counseling and personalized treatment for patients. H: Supportive health education Distribute manuals and pamphlets on the prevention and treatment of depression in the elderly. Regularly carry out group discussions and lectures for patients and their principle caregivers. Open a psychological consultation platform on the Internet. Cooperate with CHS to establish an LLD rehabilitation self-help group and organize group activities regularly. (group therapy will be conducted once a month, and family and individual therapy will be conducted at least twice a month)
Method	Make physical examination appointments or temporary on-site appointments with patients and their principle caregivers. Collect patient health information and establish health management files. Health assessment and prediction, with a detailed intervention plan. Pre-intervention training. The project leader and main group members will conduct unified training for follow-up CHS members. The main content of the training will pertain to symptoms and condition assessments, medication and efficacy observations, physical and mental health recording, interviewing skills, psychosocial intervention methods, and home visits and telephone follow-up skills. Intervention. The follow-up members should strictly follow the intervention outline formulated by the research group and adopt the supportive PDH method to complete the intervention. The project team will arrange fixed personnel to supervise and guide the members regularly. Overall, the intervention will last 6 months. Follow-up. In the first 3 months after the intervention, a monthly home visit and a telephone follow-up will be conducted. A telephone follow-up will be conducted every 2 weeks for the next 3 months, where the follow-up period will last 6 months. During each follow-up, it is necessary to evaluate the health management status of the patients and any intervention goals that have been achieved, while devising new goals based on the actual situation, and providing corresponding individual counseling according to the patients' mastery of relevant knowledge, skills, and personal needs.

Considering that Shenyang, the capital of Liaoning, has the second-largest elderly population in the province, a multi-stage sampling method will be applied during this phase as well. At the first stage, one district and one township will be randomly selected by randomized sortition in Shenyang. At the second stage, one urban community and one village community will be randomly selected from each selected district/township. At the third stage, with the help of local community health workers, 60 elderly patients with LLD who meet the inclusion criteria will be selected from each selected urban community and village community with a convenient sampling method.

In addition, the 60 elderly patients in the trial and control groups will receive clinical visits at the baseline and after 6, 9, and 12 months post-intervention using scales and questionnaires. The primary treatment and intervention outcome evaluation index shows the change in the total Geriatric Depression Scale (GDS) score. A secondary index includes the change in the total Older People Quality Of Life (OPQOL) score, the 36-item short-form (SF-36) from the Medical Outcomes Study (MOS), the Social Disability Screening Schedule (SDSS), the Family APGAR Scale, the Montreal Cognitive Assessment (MoCA), the Knowledge-Attitude-Practice (KAP) for LLD, the General Self-Efficacy Scale (GSES), and the Irritational Beliefs Scale (IBS). That is, the effectiveness of the supportive PDH intervention will be comprehensively evaluated in terms of depressive symptoms, QOL, and social, family, and cognitive functioning. See **Figure 1** for a detailed overview of the research procedure.

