## Introduction

Late life depression (LLD) is complex, burdensome, and difficult to treat. Specifically, it refers to elderly people who, for the first time in their lives, meet criteria for major depressive disorder (MDD) or display clinically significant depressive symptoms such as functional disability, cognitive decline, increased risk of medical comorbidity (e.g., co-dementia), and even suicide in severe cases (1–4). Meanwhile, MDD in the elderly, as defined by the Diagnostic and Statistical Manual of Mental Disorders, Fourth Edition, Text Revision (DSM-IV TR), has been a growing public health concern, and it is projected to be the second leading cause of disease by the year 2020 (5, 6). Epidemiological surveys reported the prevalence of MDD in elderly adults in different countries, such as the USA at 16% (7), England at 8.7% (8), and India at 24.1% (9), with considerable regional variation. Additionally, the results of a meta-analysis based on 28 studies and 76,432 subjects showed that the point, 12-month, and lifetime overall prevalence of MDD in elderly adults was, respectively, 2.7%, 2.3%, and 2.8% in China (10).

Evidence shows that successful antidepressant treatment is one of the most effective ways of reducing disability, preventing morbidity, and improving quality of life (QOL) in older patients (11). However, the response rate to an antidepressant trial with adequate dose and duration is often inadequate, and can be as low as 30%~40% in LLD patients (12). Moreover, studies have found that it is difficult to improve the cognition and personality traits of elderly patients with pharmacotherapy alone, and a number of adverse events (e.g., cardiovascular, gastrointestinal, and anticholinergic complications) are often associated with antidepressant use. Frequently, this leads to discontinuation, which contributes to a high recurrence rate and mortality (13, 14). Thus, various forms of non-pharmacological therapies with negligible side effects are being embraced by patients, such as meditation, motor therapy, cognitive behavioral therapy, interpersonal psychotherapy, reminiscence therapy, alternative therapies, and group or educational activities (15–19). These treatments are tailored to the abilities of elderly patients and target multiple contributing factors with the aim of alleviating loneliness and comorbid anxiety, enhancing social support, and improving QOL.

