### Sample Size, Power, and Effect Size

The primary goals of this study are to analyze the epidemiological characteristics and construct a risk model for LLD in Liaoning. The study design for this part is a cross-sectional study. Wang et al. reported the prevalence of MDD in elderly Chinese at 2.8%, where the ratio of urban to rural was 1.4:1 (10). That is, if the testing level α and the relative error ϵ are set to 0.05 and 0.15P, 6179 community-residing elderly adults are expected to enroll, according to the following equation (32):

$$\text{N}=[Z_{a/2}^{2}P(1-P)]/\epsilon^{2}$$

Given that 10% of the data are missing, a total of 6,800 elderly residents (approximately 3414 urban residents and 3,386 rural residents) should be included.

The secondary goals of this study are to conduct and evaluate integrated supportive PDH interventions and TAR for the objects in the trial group and control group, respectively. The study design for this part is an experimental study, and the sample size can be determined by the change in the value of the mean and standard deviation of the depression score of elderly patients before and after intervention in a previous study (33). That is, if the testing level α and type-II error β are set as 0.05 and 0.10, respectively, the sample size of the trial group and control group will be roughly 25 in both cases, according to the following equation (32):

$${\text{N}}_{1}={\text{N}}_{2}=2[\frac{({\text{z}}_{\alpha /2}+{\text{z}}_{\beta })\sigma }{\sigma }{]}^{2}$$

Given that 20% of the data are missing, each group should have a sample size of 30 LLD patients. Meanwhile, to facilitate the compliance of patients in the later intervention stages, and to ensure the effectiveness of the intervention, each patient’s primary caregiver will be required to accompany the participant. In the later stages, we will further revise the sample size according to the preliminary experimental results from the intervention study.

The participants, method, assessment time, and data collection administrators are listed in **Table 3**.

**Table 3 T3:** Data collection at baseline and follow-up evaluation.

Domain	Measure	Participants	Method	Assessment time	Administrator
Informed consent	Informed consent	All participants ^b^	Interview	Screening	Investigator
Eligibility	Inclusion/Exclusion	All participants ^b^	Interview	Screening	Investigator
Psychiatric diagnoses	MINI	All participants ^b^	Interview	Screening	Investigator

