## Discussion

Based on an analysis of the current clinical report results, there are many basic studies and investigations of the pathogenic factors of LLD. Investigations mainly focus on three groups of variables. First, researchers study the correlation between the characteristics (34, 35) (biological factors such as disease course, classification, demographics, etc.) of the disorders and their occurrence and development. Second, there is a focus on psychological factors (36, 37) (personality traits, attribution and coping style, self-esteem, etc.) and how they act on the occurrence and development of the disease. Third, researchers consider the relationship between social factors (38–40) (stressful life events, family environment, social support, marital status, economic income level, etc.) and the occurrence and development of the disease. To some extent, these studies have revealed the relationship between LLD and various influential factors, and they have identified the related variables that can predict the condition and outcome of LLD. However, few studies provide a new perspective for studying the process of integrating multiple influential research variables, while analyzing the path of interaction between variables and exploring the influence of various factors on the overall research. In our study, therefore, biological, psychological, and social factors will be integrated to analyze and predict LLD risk factors. In addition, the results will be incorporated into the system of occurrence and development of the disorder. Then, SEM of the risk factors for LLD will be constructed. Furthermore, in view of differences in the prevalence of LLD between rural and urban areas, participants will be recruited from both rural and urban sites for a broadly inclusive and representative elderly population that ensures the equilibrium of sample sources. In doing so, the results and conclusions of the study will be widely generalizable.

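### The prevalence survey is sized as a simple random sample but recruits by convenience from only 8 or 16 communities, so neither the ±15% precision nor the representativeness claim is supported

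*Protocol article*

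**What the plan says.** In the protocol article, *Sample Size, Power, and Effect Size* makes the survey the primary goal and sizes it with N = Z²P(1−P)/ε². The inputs are "the prevalence of MDD in elderly Chinese at 2.8" per cent and a half-width tied to it: "if the testing level α and the relative error ϵ are set to 0.05 and 0.15P". This gives 6179, and then: "Given that 10% of the data are missing, a total of 6,800 elderly residents". The total is split almost equally, 3,414 urban and 3,386 rural.

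*Enrollment, Supportive PDH Intervention, and Follow-Up* describes a multi-stage sample. Four cities are drawn; then "one district and one township will be randomly selected from each selected city"; then communities are drawn within each. At the last stage "elderly residents will be selected from each selected urban community and village community with a convenient sampling method". The same paragraph gives balance and representativeness as the purpose of the scheme, and the *Discussion* says that "the results and conclusions of the study will be widely generalizable".

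*Data Preprocessing and Statistical Analysis* names t-tests, Mann–Whitney and chi-squared tests, correlation, logistic and linear regression, and structural equation modelling (SEM). It mentions no weights, cluster term or design-based variance.

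**The concern.** The sizing formula holds when people are drawn independently and with equal probability. Here they come in blocks of several hundred from a handful of communities. If depression is even slightly more common in some communities than in others, the blocks carry less information than their headcount suggests. The primary deliverable, a prevalence for Liaoning, would then be reported more precisely than the design allows. The same applies to tests of factors that differ between communities, and some of those tests decide which variables enter the SEM.

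The last stage raises a separate problem. Under convenience selection nobody's probability of inclusion is known. No variance formula, and no increase in numbers, makes the resulting interval valid for the provincial population.

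**Working it through.** **Inputs from the article.** P = 2.8%, two-sided α = 0.05 (z = 1.96), ε = 0.15P, N = 6179 before and 6,800 after the 10% allowance. The sampling stages give 4 × 2 = 8 districts or townships. The third-stage wording allows one community in each (8) or one urban and one village community in each (16). **Not in the article:** the ICC. I assume 0.001 to 0.01.

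**1. The article's own figure.** 1.96² × 0.028 × 0.972 / (0.15 × 0.028)² = 5,927, not 6179. P = 2.7%, which the *Introduction* gives as the point prevalence, yields 6,153; z = 2 with P = 2.8% yields 6,171. The step to the final total is 6179 × 1.1 = 6,797, rounded to 6,800. The mismatch at 2.8% is a separate minor point, and nothing below depends on it. No variant contains a clustering term.

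**2. Evaluable numbers.** 6,800 × 0.9 = 6,120, or 765 per community with 8 communities and 382.5 with 16. Under simple random sampling the relative error is 1.96 × √(0.972 / (0.028 × 6,120)) = 14.8%, so the target would be met.

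**3. With clustering.** Design effect DE = 1 + (m − 1) × ICC. Relative error = 1.96 × √(DE × 0.972 / (0.028 × 6,120)) = 14.8% × √DE.

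| Assumed ICC | 16 communities: DE, effective N, relative error | 8 communities: DE, effective N, relative error |
|---|---|---|
| 0.001 | 1.38, 4,430, 17% | 1.76, 3,469, 20% |
| 0.002 | 1.76, 3,471, 20% | 2.53, 2,421, 23% |
| 0.01 | 4.82, 1,271, 32% | 8.64, 708, 43% |

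For scale, an ICC of 0.001 is a between-community standard deviation of √(0.001 × 0.028 × 0.972), about 0.5 percentage points around 2.8%.

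**4. Where ±15% stops holding.** It needs DE ≤ 6,120 / 5,927 = 1.033, so ICC ≤ 0.033 / (m − 1): about 0.00009 with 16 communities and 0.00004 with 8. If all 6,800 were evaluable, DE could reach 6,800 / 5,927 = 1.147, and the limits would be about 0.00035 and 0.00017.

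**5. More people in the same communities.** As m grows, the relative error tends to 1.96 × √(ICC × 0.972 / (0.028 × c)) for c communities. This exceeds 15% once the ICC is above 0.0027 (c = 16) or 0.0013 (c = 8), however many are recruited.

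**6. Effect on tests.** For a factor that is constant within a community, a nominal 5% test that ignores clustering has true size 2(1 − Φ(1.96/√DE)). That is about 10–14% at ICC 0.001 and 37–51% at ICC 0.01.

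**The case against.** **The ICC is assumed.** This is true: the article gives none, and the size of the loss depends on it. At 0.001 the error is 17–20%, a moderate shortfall. What stands is the threshold in step 4, which is so low that almost any variation between communities breaks ±15%. The simple DE formula also ignores that urban/rural status is fixed by design within each city, so it is an approximation.

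**Weights and variance methods may sit in a fuller plan.** They may, and the listed tests do not rule them out. But the sizing formula, the sampling stages and the representativeness claim are all stated here and do not fit together. A later analysis plan cannot turn convenience selection into probability sampling.

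**The limitations already restrict generalization.** The *Discussion* limits it because the sample comes only from Liaoning. It says nothing about convenience selection or clustering within Liaoning.

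Three stronger readings are tempting, and the document does not support them:

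- *All risk-factor p-values are too small.* Many listed factors are individual-level, such as coping style, personality and sleep. Where a factor varies mainly within communities, the inflation may be small. The case is firm for urban/rural status and local mental health resources.
- *Housebound or withdrawn elders are missed.* *Organizational Structure* allows completion at elderly residences as well as in public activity areas, and it describes where the survey is completed, not where people are recruited.
- *The error reaches 46% at ICC 0.01.* That figure pairs 850 enrolled people per community with 6,120 evaluable people overall. On one consistent basis the upper end is 43%.

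**Conclusion.** The point holds. The survey's stated precision belongs to a simple random sample, which is not what the article describes. At 6,120 evaluable people and P = 2.8%, the relative error is about 17–20%, 20–23% and 32–43% for assumed ICCs of 0.001, 0.002 and 0.01. In each pair the lower figure is for 16 communities and the higher for 8. The direction is certain for any positive ICC; the size is conditional on the assumed range.

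Anti-conservative testing is established only for factors that vary between communities. The claims of representativeness and wide generalizability are unsupported because the last stage has unknown selection probabilities. That problem is independent of the ICC, and no design effect covers it.

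**What to change.** 1. **Precision.** In *Sample Size, Power, and Effect Size*, replace ±15% with the relative error implied by a design effect over a stated ICC range, and say whether there are 8 or 16 communities.
2. **Analysis.** Estimate prevalence with urban/rural population weights, since the near-equal split is an allocation and the article gives no population shares. Analyse prevalence and risk factors with community as the cluster, using a small-sample correction (such as a t reference with few degrees of freedom) or a community random effect. Plain cluster-robust variance is unreliable with 8–16 clusters. If each city has only one community per urban or rural cell, say that variation between communities within a cell cannot be estimated.
3. **Selection.** Either draw residents at random from community resident lists where these can be obtained, or remove the representativeness and wide-generalizability claims and list convenience selection as a limitation. The article does not establish that usable lists exist. The eligibility rules on *hukou* status and five-year residence make the question worth asking.

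**Cost.** A less favourable stated precision, wider intervals and a little more analysis work; list-based selection, if chosen, adds fieldwork. No larger sample is required, and recruiting more people in the same communities would not restore ±15% once the ICC exceeds the limits in step 5.

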### Study Design

This is a multi-stage and prospective study. It includes the following three stages:

The first stage is a cross-sectional study, based on the baseline information from 6,800 community-dwelling elderly adults collected through a set of questionnaires. The aim of the first stage is to investigate the epidemiological characteristics of LLD in northern China, and to explore the biological, psychological, and social risk factors for developing LLD.The second stage involves statistical analysis, with the aim of constructing a risk factor model for LLD and analyzing direct and indirect functional routes on the basis of structural equation modeling (SEM).The third stage is an experimental study, comprising a 6-month supportive intervention period and a 6-month follow-up period. In order to ensure the participation of the subjects in this study and improve the effectiveness of the interventions, a total of 60 elderly patients with depression and their principle caregivers will be randomly and equally assigned to trial and control groups.

Trial group patients and caregivers will undergo supportive PDH interventions, and control group patients and caregivers will receive TAR. Subsequently, depressive symptoms, QOL, and the social and cognitive functioning of the patients in the two groups will be respectively assessed at a baseline and after 6, 9, and 12 months post-intervention by using scales and questionnaires to analyze the effectiveness of the supportive PDH intervention measures. Ultimately, an SIHM model will be constructed by combining PDH intervention with mental health institutions, CHS, and aging families as the main line.

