### Data Preprocessing and Statistical Analysis

The statistical analyses will be performed by employing the SPSS statistical package, version 20.0 (SPSS Inc., Chicago, IL, USA), and all evaluations of significance will be determined based on two-sided tests using the 0.05 level of statistical significance. In addition, missing values will be replaced by the column mean/median in this study. The details of the analytic approach are as follows.

Demographic and clinical characteristics, lifestyle patterns, medical history, history of alcohol and drug abuse or dependence, family history of mental illness, self-knowledge and treatment attitude, and the self-efficacy levels and depressive symptoms of the subjects will be described by frequency distribution, percentage, arithmetic mean, and standard deviation.Comparison of the above variables between patients with or without LLD will be made using the independent-sample *t*-test, Mann–Whitney *U*-test, and the chi-squared test, as appropriate.Correlation analysis, logistic regression (for binary variables), and multiple linear regression (ANCOVA for continuous variables) will be used to determine whether the variables can enter SEM, and to test the direct and indirect pathways among these hypothesized determinants.Amos version 22.0 statistical software will be used for SEM of the risk factors for LLD.GDS, SDSS, SF-36, OPQOL, Family APGAR, GSES, IBS, MoCA, and the related KAP for LLD in the elderly will be used as evaluation indices, and analysis of variance (ANOVA) will be applied to compare the results of the control and the trial groups before and after intervention.Regression analysis will be used to analyze the influence of various factors on the effectiveness of the supportive PDH intervention.

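### The plan guarantees that the randomised arms will show no statistical differences at baseline, which random assignment cannot guarantee and which would not in any case amount to balance

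*Protocol article*

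**What the plan says.** The Study Design section of the Protocol article says that "a total of 60 elderly patients with depression and their principle caregivers will be randomly and equally assigned to trial and control groups". The Abstract also describes the assignment as random.

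The section Enrollment, Supportive PDH Intervention, and Follow-Up then adds a condition on the result of that assignment: "we will ensure that there are no statistical differences between the two groups in term of the degree of depression". The sentence goes on to list "drug treatment programs, knowledge of mental health, geographic distribution, and other aspects before carrying out the interventions". That makes four named variables (degree of depression, drug treatment, knowledge, geography) and an unspecified remainder, all to be settled before treatment begins.

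The only criterion given anywhere for a statistical difference is the general rule in Data Preprocessing and Statistical Analysis: "all evaluations of significance will be determined based on two-sided tests using the 0.05 level of statistical significance". That section compares the arms before and after intervention by analysis of variance and names no baseline covariate for the comparison. The primary outcome is the change in total GDS score. Table 3 shows GDS collected at baseline and at every follow-up, by investigator interview.

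**The concern.** The article commits to an outcome of the allocation and does not merely describe how baseline data will be reported. Chance differences belong to randomisation, so a promise that none will be significant must sometimes fail unless something acts on the allocation. The article does not say what acts, who acts, or which variables fall under the open-ended remainder.

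This stage is the study's only randomised comparison. It has 30 patients per arm, who are found by convenience sampling with the help of community health workers, and its primary outcome is taken by interview. If the groups could be rearranged at someone's discretion after baseline severity is known, the protection that randomisation gives against selection bias would be lost, and no analysis could restore it.

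There is a second difficulty. A non-significant test in 60 patients says little about whether the arms are alike, so the promise could be kept to the letter and still leave a material imbalance.

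**Working it through.** **Inputs from the article.** Assignment is random and equal, 30 per arm. The test level is 0.05, two-sided. Four variables are named, plus others. The sample size calculation (section Sample Size, Power, and Effect Size) uses alpha 0.05 and 90% power and arrives at about 25 per arm. An allowance for loss is then added: "Given that 20% of the data are missing, each group should have a sample size of 30 LLD patients".

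**The plan's own figure.** The 25 per arm cannot be reproduced, because the difference and SD taken from the previous study are not given. Working backwards, (1.960 + 1.282) × sqrt(2/25) = 0.917, so 25 per arm implies an effect of about 0.92 SD of whatever score was used. The 30 follows as 25 × 1.2. Only the 30 per arm is needed below.

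**Step 1: how often a correct randomisation breaks the promise.** For k independent tests at 0.05, the chance of at least one significant difference is 1 − 0.95^k.

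| Variables tested | Chance of at least one significant difference |
|---|---|
| 4 (those named) | 1 − 0.8145 = 18.5% |
| 5 (the remainder counted as one) | 22.6% |
| 10 (assumed reading of the remainder) | 40.1% |

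Independence is an assumption. For four tests each at exactly 0.05, the figure lies between 5% (complete dependence) and 4 × 0.05 = 20% (the Bonferroni bound). Suppose instead that stratification made failure impossible on two of the four. The other two would still give 1 − 0.95^2 = 9.75%, before any unnamed variable is counted.

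**Step 2: what a non-significant test lets through.** The largest standardised difference that passes a two-sided t-test is t(0.975, 2n − 2) × sqrt(2/n).

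- At n = 30: 2.002 × 0.2582 = 0.517 SD.
- At n = 25: 2.011 × 0.2828 = 0.569 SD.
- For a binary factor (uncorrected chi-squared test, 30 v 30), 10/30 v 17/30, or 33% v 57%, passes.

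In 200,000 simulated randomisations of 30 v 30 with a normal baseline variable, 29% had a difference above 0.25 SD and still passed, and 20% had one above 0.30 SD. These two thresholds are illustrative and do not come from the article.

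**Step 3: the effect of a blind redraw on the test.** Suppose the allocation were redrawn, without discretion, until the baseline tests were non-significant. The type I error of an unadjusted test at nominal 0.05 was simulated with 40,000 runs per setting. The baseline–outcome correlations are assumed.

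| Rule | Outcome analysed | Correlation | Type I error |
|---|---|---|---|
| One baseline test | Post-intervention score | 0.3 / 0.5 / 0.7 | 0.046 / 0.045 / 0.036 |
| Four baseline tests | Post-intervention score | 0.5 / 0.7 | 0.042 / 0.036 |
| Four baseline tests | Change from baseline | 0.5 / 0.7 | 0.044 / 0.047 |

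The test becomes slightly conservative. The redraw also narrows the baseline difference a little: its SD falls from 0.26 to 0.23.

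**The case against.** The strongest defence is that the sentence is loose wording for an intention to balance the groups. The article condenses a fuller protocol, and the details of stratification, minimisation or constrained randomisation may be given there. This stands in part. The absence of those details is no fault, and none is claimed. It does not rescue the sentence, because stratification and minimisation improve balance on chosen factors without guaranteeing non-significance on unnamed ones. Constrained randomisation on a closed, pre-specified list could meet such a criterion, but none is described and the list is left open.

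Several stronger readings are tempting, and the article does not support them:

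- **Patients will be swapped, dropped or redrawn after allocation.** A reader might infer this from the guarantee and its timing. The article names no such procedure, nor is that the only conceivable way to meet the criterion.
- **The false-positive rate is inflated.** Under a blind redraw it falls slightly (step 3). Bias arises only if reallocation is discretionary.
- **One correct allocation in four would be altered.** The four named variables give about one in five showing a difference, and the article does not say that any allocation would be altered.
- **A passing imbalance is over half the design effect.** Comparing 0.52 SD with 0.92 SD may mix scales. The sample size rests on a before-and-after change in depression score, whose SD need not be the baseline GDS SD. Since the outcome is also a change score, a baseline gap need not carry over one for one.

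It is also true that the sentence does not cause imbalance. Simple randomisation allows the same differences and, in 5% of cases, larger ones, so deletion alone would not improve balance.

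**Conclusion.** The sentence is wrong as written. A guarantee of no statistical differences on four named variables and an open-ended remainder conflicts with the random assignment stated in the same article. About 18.5% of correct allocations would break it on the named variables alone, assuming four independent tests at 0.05. The use of that level rests on the article's general significance rule, since the sentence names no test. How the promise would be kept is not stated, so selection bias is a conditional risk and not a demonstrated one.

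The criterion is also a poor guide to balance, because at 30 per arm it passes any difference up to 0.52 SD. Adjusting the arm comparison for baseline GDS is a separate, free improvement, since GDS is already measured at baseline.

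**What to change.** 1. Delete the guarantee in the Enrollment section.
2. State that no patient is reallocated, swapped or dropped after assignment because of baseline differences.
3. Seek balance by design. Use a concealed list stratified on a few named factors already collected, for example urban/village community and baseline GDS (high/low), with random blocks. These two factors give four strata averaging 60/4 = 15 patients. Minimisation with a random element is an alternative.
4. Describe baseline characteristics by arm without significance tests.
5. Compare GDS between arms with a model adjusted for baseline GDS and the factors used in the allocation, in place of the unadjusted analysis of variance.

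The choice of factors is the sponsor's; those named are examples. The cost is an allocation list prepared in advance, a few changed sentences and one changed analysis model, with no extra patients, visits or measurements.
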